### Trial data management

Research Electronic Data Capture (REDCap), a secure web platform for building and managing online databases and surveys, will be used for managing the trial data. The REDCap mobile app will be used to collect the required data for the CRF designed in the app. Screening forms will be programmed to collect data for differentiating eligible and non-eligible patients. At the screening stage, participants who meet all inclusion criteria and do not meet any exclusion criteria will be eligible to take part in the study. They will be given the participant information sheet and consent form. If they consent to take part in the study, their demographic details (including active mobile number) will be recorded on the REDCap database.

The mTB-Tobacco app will be linked to the REDCap server through API (Application Programming Interface) which will capture the patient trial ID along with the mobile numbers to send SMS text messages as per the defined schedule. The eligible and consented participants belonging to the intervention arm will receive the SMS messages, whereas those belonging to the control arm will not receive any SMS. Figure 3 gives a flowchart of data management procedures.

**Figure 3 F3:**
[figure not shown]
Flowchart of procedure of data management. CXR, chest X-ray; eCRF, electronic case report form; RA, research assistant; REDCap, Research Electronic Data Capture; TB, tuberculosis.

The data collection will consist of responses to a set of translated and structured questionnaires in the electronic CRFs (eCRFs) which will be completed and facilitated by the field research team. The data entered will synchronise with the database on a secured server. De-identified data merged for study sites for separate eCRF and wide format data combining different eCRFs through matching and merging will be shared via Edinburgh DataSync with the trial statistician who will conduct the analysis.

Overall data quality will be ensured through training and supervision by the respective country trial team. Quantitative data once synced in the server will also be peer-reviewed by the statistician. The trial management team and country teams jointly will develop a detailed data management plan to ensure data safety and quality.

### Sample size

The study requires a total of 2700 smokers newly diagnosed with pulmonary TB (∼43 recruits from 63 TB centres, the clusters) assuming that 20% might not provide primary outcome data. This sample also includes the first 16 participants taking part in the pilot study, in case the intervention needed major refinement then we would be unable to use their data.

The required sample size for the superiority trial (phase 3) was determined by using a power of 90%, a significance level of 5% and expected abstinence rates of 18% for mTB-Tobacco and 8% for normal treatment after 6 months.^13^ The study will comprise a total of 27 TB centres, considering the ratio of intervention to control as 2:1. After considering a 20% attrition rate, it was determined that the sample size would be 704 participants. This would result in an average of around 26 individuals in each cluster. Given that the study will be carried out as a cRCT with an intracluster correlation coefficient of 0.02,^19^ the design effect was computed to be 1.50. This results in an effective sample size of around 1080 people (or 40 subjects per site).

In the non-inferiority trial (phase 4), considering 90% power, one-sided hypothesis and 2.5% significance level to establish non-inferiority of mTB-Tobacco intervention to face-to-face behavioural support, comparing 18 clusters in each treatment arm assuming face-to-face achieved 18% abstinence at 6 months and the non-inferiority margin was 8%. Assuming that just 2% would give up with no intervention at all, the established treatment effect of face-to-face behaviour support over natural cessation over 6 months would then be 16% (18–2%). The non-inferiority margin of 8% equates to the mTB-Tobacco intervention preserving at least 50% (8/16) of the established treatment effect of the face-to-face intervention. The above-mentioned sample size assumptions will be checked midway through the recruitment period, and the sample size will be adjusted accordingly. Considering a 20% attrition rate, the final sample size was determined to be 1036 participants, resulting in approximately 29 participants per cluster across 36 clusters (18 in each arm). The design effect was calculated to be 1.56, yielding an effective sample size of approximately 1620 subjects (or 45 subjects for each site). Further adjustments to the sample size assumptions will be made midway through the recruitment period as needed. Sample size details for superiority and non-inferiority trials are given as online supplemental figure 1.

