## Discussion

This trial will be the first one to test the effectiveness of mHealth-based mTB-Tobacco intervention to help patients with TB quit smoking at 6 months. The sample size is appropriately calculated keeping in mind the cluster design and design effect to appropriately power this trial to test the primary objective. The mHealth-based interventions are promoted by policymakers due to low resource requirements. An effective mTB-Tobacco intervention could be transformational for patients with TB who smoke. It will not only benefit the patients with TB but will also allow the NTPs to have a less resource-intensive and effective intervention for smoking cessation that can be easily integrated into their system. A shift from paper-based TB recording and reporting systems to a digital system in Pakistan and Bangladesh makes it easier to integrate mHealth intervention into the existing system.

To date, all evidence-based smoking cessation interventions, face-to-face behaviour interventions, nicotine replacement therapies and pharmacotherapy-based interventions have failed to be integrated into existing TB control programmes. A case study was published where challenges of integrating tobacco cessation interventions in TB programmes were explored in the context of Pakistan and Nepal.^14^ The main challenges that were highlighted in the study included health professionals’ doubts about the contextual relevance of interventions, non-conducive environments, political reluctance to change, workload of TB staff, motivation of TB staff and capacity to deliver cessation intervention and inadequate training and support during intervention implementation.^14^ Several of the above-mentioned issues can be resolved through a digitally delivered intervention. For instance, the TB staff would not have to perform any extra task out of their routine to deliver the intervention as the SMS messages are delivered to the patient with TB’s personal mobile phone number through an automated system. In future, the digital app can be further improved by making it interactive instead of just one-way delivery. It can also be personalised for every patient with TB who wants to quit smoking by using artificial intelligence tools. The cost of the intervention will be one-off, for example, the web portal that will be developed under this project can be used by TB programmes with no to minimal extra cost to only account for the SMS text message delivery.

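### Phase 4 is stated to have 90% power, but its starting figure of 1036 gives 85% before clustering and the planned 1620 give about 80%

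*Protocol article*

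**What the plan says.** The Sample size section of the protocol article gives the phase 4 inputs as "considering 90% power, one-sided hypothesis and 2.5% significance level", "assuming face-to-face achieved 18% abstinence at 6 months and the non-inferiority margin was 8" percentage points, and 18 clusters in each arm. No separate mTB-Tobacco rate is given for phase 4; the phase 3 paragraph has "expected abstinence rates of 18% for mTB-Tobacco and 8% for normal treatment after 6 months". The ICC of 0.02 also appears only in the phase 3 paragraph.

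The chain of results is: "Considering a 20% attrition rate, the final sample size was determined to be 1036 participants", or about 29 per cluster in 36 clusters, and then "The design effect was calculated to be 1.56, yielding an effective sample size of approximately 1620 subjects (or 45 subjects for each site").

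The section also provides for a check of the sample size assumptions midway through recruitment, with adjustment as needed. The Discussion tells the reader: "The sample size is appropriately calculated keeping in mind the cluster design and design effect".

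**The concern.** Two things do not fit. The starting figure of 1036 looks too small for 90% power at a one-sided 2.5% level. The design effect uses the cluster size before inflation, although the number of centres is fixed, so the inflation makes each cluster larger and raises the design effect again. Both push true power below the stated value.

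Phase 4 tests the claim that text messages are non-inferior to face-to-face support. If power is nearer 80% than 90%, a failure to show non-inferiority is more likely than the text admits even when the two interventions are equally effective. Such a result could be misread as evidence of inferiority from a well-powered trial. The false-positive risk is not affected.

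**Working it through.** **Inputs.** Abstinence 18% in both arms (face-to-face from the phase 4 text; mTB-Tobacco carried over from phase 3, so a true difference of zero); margin 0.08; one-sided 2.5% (z = 1.960); attrition 20%; 18 centres per arm; 45 recruits per centre. The ICC of 0.02 is stated for phase 3, and the phase 4 design effect implies the same value: (1.56 − 1)/(29 − 1) = 0.02.

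**Step 1: size before clustering.** n per arm = (1.960 + z_power)² × 2 × 0.18 × 0.82 / 0.08².

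- 90% power: 484.7 per arm. 484.7/0.8 rounds up to 606 per arm, or 1212 in total.
- 85% power: 414.1 per arm. 414.1/0.8 = 517.7 rounds up to 518 per arm, or 1036 in total.

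The plan's 1036 is thus reproduced exactly at 85% and is about 15% below the 90% answer. Run forwards, 1036 × 0.8 = 828.8 analysed gives 85.0% power with no clustering.

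Other conventions at 90% power do not give 1036:

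- multiplying by 1.2 for attrition: 1164
- Farrington-Manning: 1225
- continuity-corrected non-inferiority formula: 1273
- one-sided 5%: 990

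Two calculations outside the stated design come within 3%: a continuity-corrected superiority test of 18% against 10% (1045), and a continuity-corrected non-inferiority formula that ignores attrition (about 1019). Neither uses the stated inputs, and neither changes what 1036 delivers under them.

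**Step 2: design effect.** The plan's figures reproduce: 1036/36 ≈ 29; 1 + 28 × 0.02 = 1.56; 1036 × 1.56 = 1616, rounded to 36 × 45 = 1620. But the clusters will hold 45 recruits, of whom 45 × 0.8 = 36 are analysed:

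- on analysed patients, 1 + 35 × 0.02 = 1.70
- on recruited patients, 1 + 44 × 0.02 = 1.88

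**Step 3: power of 1620.** Analysed: 1620 × 0.8 = 1296, or 648 per arm. Effective n per arm = 648 / design effect; SE = √(2 × 0.18 × 0.82 / effective n); power = Φ(0.08/SE − 1.96). The t version uses a noncentral t with 34 degrees of freedom (36 centres − 2).

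| Design effect | Effective n per arm | SE | Power, normal | Power, t |
|---|---|---|---|---|
| 1.56 (as stated) | 415 | 0.0267 | 85% | 83% |
| 1.70 (36 analysed) | 381 | 0.0278 | 82% | 80% |
| 1.88 (45 recruited) | 345 | 0.0293 | 78% | 76% |

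If nobody were lost, 1620 with 1.88 would give 86% (normal).

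**Step 4: dependence on the ICC.** Normal approximation, with the cluster size taken at 45 and then at 36:

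- ICC 0.01: 88% to 90%
- ICC 0.02: 78% to 82%
- ICC 0.03: 69% to 74%

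**Step 5: what 90% would take with 36 centres and ICC 0.02.** With m analysed per centre, solve 18m / (1 + (m − 1) × 0.02) = 484.7. This gives m = 57.2, so 57.2/0.8 = 71.5 recruits per centre and about 2,570 in total. Rounding up to 58 analysed gives 72.5 per centre, or 2,610. On the t basis, about 66 analysed per centre are needed: 66/0.8 = 82.5 recruits, or about 2,970.

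**The case against.** The strongest reply is that the plan provides for a midway check and adjustment. That bears on the consequences, but the check is of the assumptions. If 18%, 20% attrition and an ICC of 0.02 all prove right, it gives no reason to change anything, and power is still about 80%. A revision made with the same formula would carry the same error.

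A second reply is that the planned analysis is a mixed-effects logistic model with covariates, after minimisation on country and patient volume, so a comparison on 34 degrees of freedom may be too strict. This stands, and it is why a range is given rather than a single value. The normal figure of 82% is still short of 90%.

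Third, the ICC is uncertain, and at 0.01 the stated power is nearly met. But the plan's own value is 0.02, and the error can as easily run the other way.

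A reader might infer more than the article supports:

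- **That 85% was the power actually used.** This is an inference from the exact match. The article never mentions 85%, and the supplemental figure with the sample size details is not shown.
- **That power collapses to about 60% because the Introduction cites quit rates up to 41%.** That is an upper figure from earlier trials. Putting both arms there challenges an assumption, not this arithmetic, and nothing in the article plans for it.
- **That phase 3 is equally affected.** It makes the same cluster-size slip ("the design effect was computed to be 1.50", from 26 per centre although 40 are recruited), but its power stays near 90% (87% to 93% depending on the test).

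**Conclusion.** The stated 90% is wrong as written. With the plan's own inputs, 1036 gives 85% power before clustering, and 90% would need 1212. With the design effect taken at the cluster size the trial will have, 1620 recruits give about 80%: 82% (normal) or 80% (t) at 1.70, and 78% or 76% at 1.88. The claim fails even with the stated 1.56, at 85%. The miss rate is thus roughly 18% to 24% instead of 10%. Saying that it exactly doubles would pick one point from that range.

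This rests on 18% in both arms, 20% attrition, an ICC of 0.02 (stated for phase 3 and implied for phase 4) and equal cluster sizes. The Discussion's assurance about the design effect does not hold for phase 4. Calling 1620 an effective size is a wording slip; it is the inflated size.

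**What to change.** Keep 1620 and correct the text of the phase 4 paragraph:

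- Restate power as about 80% (76% to 82% at ICC 0.02), with the sensitivity by normal approximation: 88% to 90% at ICC 0.01 and 69% to 74% at ICC 0.03.
- Give the design effect as 1.70, based on 36 analysed per centre.
- State that the starting figure of 1036 corresponds to 85% power.
- Call 1620 the inflated size.
- Require the midway sample size check to use the corrected design effect.
- Amend the matching sentence in the Discussion.

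This costs wording and a less favourable power statement, but no extra patients.

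Do not insert 1212 while keeping 1620, because the chain then breaks: 1212 × 1.70 = 2060, and even 1212 × 1.56 = 1891. If 90% is to be kept, the whole chain has to be re-derived for 36 centres. That gives about 72 recruits per centre (about 2,570 to 2,610 in total) by normal approximation, or about 82 per centre (about 2,970) on the t basis. The text should say which basis is used. Phase 4 starts only if phase 3 succeeds, so the choice can be made before its recruitment begins.

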### Statistical analysis

#### Descriptive statistics

Continuous outcomes will be summarised using means and SD, and categorical outcomes using frequencies and percentages across intervention and control arms.

#### Inferential statistics

A mixed-effects model will be used to assess the impact of mTB-Tobacco on continuous outcomes, incorporating fixed effects for the intervention, random effects for clusters and relevant covariates. Logistic regression within the mixed-effects framework will be used to analyse categorical outcomes, accounting for cluster-level variability and intervention effects for the analysis of data in this cRCT. At the end of phase 3 superiority trial, an interim analysis will be done by an independent statistician to assess the effectiveness of the mTB-Tobacco intervention. The result will decide whether the trial needs to proceed to phase 4 non-inferiority trial or be terminated early. In this study, the missing data patterns will first be examined to determine whether the missingness adheres to patterns of complete randomness, randomness or non-randomness. Multiple imputation, a robust technique that generates multiple data sets with imputed values for missing observations, will be used to address the missing data. As a sensitivity analysis technique, missing data imputation will be used to evaluate the robustness of our findings.^20^ The estimates of the intervention effect will next be compared between analyses carried out with complete case analysis and analyses using imputed data sets. This will improve the validity of the study’s conclusions by enabling an assessment of the effect of missing data on the estimation of intervention effects in this cRCT. Open-source R Project software and JASP Team (2024; V.0.19.3) computer software will be employed as our primary tools for data analysis.

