### Randomisation

Since the interventions will be delivered at the group level, this trial is designed as a cluster cRCT where TB centres will be randomly allocated to the different trial arms. The TB centres (clusters) would be randomised in a 2:2:1 ratio to mTB-Tobacco (intervention A), face-to-face (intervention B), or standard care (Control). An independent statistician, blinded to clusters, will identify and use computer-generated random number lists to generate the allocation sequence. The allocation will be based on using minimisation to ensure balance across the groups on the average number of patients with TB seen per month and geographical locations (Bangladesh and Pakistan).

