### Study outcomes

#### Primary outcomes

The primary outcome will be biochemically verified continuous abstinence at 6 months postrandomisation.^18^ Abstinence is defined as a self-report of not having used more than five cigarettes, bidis, water pipe sessions since the quit date, verified biochemically by a breath carbon monoxide (CO) reading of less than 10 ppm at month 6.^18^

In case of concomitant smokeless tobacco use, biochemical verification will be carried out using COT Rapid Test Cassette (Hangzhou All Test Biotech) to detect cotinine (a nicotine metabolite) level in urine samples. The test result will be interpreted as ‘negative’ if two lines appear (one coloured line in the control line region and another apparent coloured line in the test line region) or ‘positive’ if one coloured line appears in the control line region. The negative result will indicate that the cotinine concentration is below the detectable level (200 ng/mL) while the positive result will indicate that the cotinine concentration exceeds the detectable level (200 ng/mL). The research assistant (RA) will perform cotinine dipstick tests on urine samples collected from the patients, which will be discarded after cotinine levels have been recorded on the case report forms (CRFs).

When a patient self-reports abstinence with an elevated CO level of >10 ppm (and cotinine levels in concomitant users indicating active tobacco use), the biochemical verification will supersede the self-report and the patient will be defined as a tobacco user.

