### Study assessments

All study participants will have assessments on day 0, week 9 and month 6 time points corresponding with routine TB clinic visits. All the trial activities will be performed by field RAs (one RA per site) who will be hired and trained to take patient consent, collect baseline data, follow-up data and perform study assessments. The trial assessment schedule, given as table 2, outlines the visit dates necessary for data collection, but the patient may be seen more frequently for routine clinical care as needed. During the treatment period, if study participants are unable to attend on the day, every effort would be made to complete the visit within 2 days of the scheduled date. If a scheduled visit is missed without notice, then the RA should endeavour to contact the patient by phone or by home visit.

**Table 2 T2:** Participant enrolment and follow-up assessment schedule for Quit4TB trial

Assessment	Screening	Day 0 baseline	Week 9	Month 6
Assessment of eligibility criteria	⌧			
Written informed consent	⌧			
Face-to-face/phone-based interaction			⌧	
Self-reported tobacco use/abstinence status		⌧	⌧	⌧
CO measurement				⌧
Sociodemographic information		⌧		
Tobacco use and quit history		⌧		
Nicotine dependency		⌧	⌧	⌧
Economic outcomes		⌧		⌧
Process outcomes (fidelity)			⌧	⌧
Medication (TB) compliance			⌧	⌧
Adverse events review			⌧	⌧
TB outcomes				⌧

CO, carbon monoxide; TB, tuberculosis.

During the follow-up phase, scheduled assessments will be carried out no more than 5 days before the scheduled visit. Scheduled visits will be rescheduled to allow for public holidays or other unavoidable circumstances that affect the scheduled visit date, but the rescheduled visit should be no more than 5 days from the originally scheduled visit date. Participants will also be given a card with the contact details for the trial RA and the clinical TB care team at their site. If a patient is more than 5 days late for a scheduled study visit, an additional visit will be performed as soon as possible, including the appropriate assessments that were specified in the trial schedule for the visit that was missed.

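### The model described for the binary primary outcome names neither country nor centre volume, the two factors on which centres are minimised; adding them costs almost nothing and recovers power if quit rates differ by country

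*Protocol article*

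**What the plan says.** Protocol article, Randomisation: centres are allocated by "minimisation to ensure balance across the groups on the average number of patients with TB seen per month and geographical locations (Bangladesh and Pakistan").

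Primary outcomes: "The primary outcome will be biochemically verified continuous abstinence at 6 months postrandomisation". Each participant is either abstinent or not, so the outcome is binary.

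Inferential statistics has two model sentences. The first concerns the effect of mTB-Tobacco "on continuous outcomes, incorporating fixed effects for the intervention, random effects for clusters and relevant covariates". The second reads "Logistic regression within the mixed-effects framework will be used to analyse categorical outcomes, accounting for cluster-level variability and intervention effects". Only the first mentions covariates, and it does not list them. The Abstract also ties covariates to continuous outcomes, although it calls the model generalised linear.

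Nowhere does the article say that country or centre volume enters a model, and nowhere does it say that they are left out.

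**The concern.** When allocation forces the arms to be alike on a factor, the analysis should carry that factor. Otherwise the factor's variation, which barely affects the treatment comparison, is still counted as noise. Here a Bangladesh–Pakistan difference in quitting would be absorbed by the centre random effect and would widen the interval for the treatment effect.

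The consequence is loss of efficiency, not bias. In phase 3 an over-wide interval could miss a real effect and so stop the trial before phase 4. In phase 4 it could mean failing to show non-inferiority.

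**Working it through.** **The plan's own phase 3 figure.** The inputs are "power of 90%, a significance level of 5% and expected abstinence rates of 18% for mTB-Tobacco and 8% for normal treatment after 6 months", with 2:1 allocation, 27 centres, 20% attrition and ICC 0.02 (Sample size). I take the 5% level as two-sided. The continuity-corrected two-proportion formula gives 195 controls, so 585 in total, and 585 × 1.2 = 702 (stated: 704). The design effect is 1 + (26 − 1) × 0.02 = 1.50, and 704 × 1.50 = 1056, or 39.1 per centre, rounded up to 40 × 27 = 1080. The stated figures reproduce, so this point exposes no error in that calculation.

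**Phase 4, analytic.** There are 18 centres per arm with 45 recruited in each, so 45 × 0.8 = 36 analysed per centre and 648 per arm. Abstinence is 18% in both arms and the margin is 8 points. Total ICC is taken as 0.02, which matches the stated phase 4 design effect: 1 + 28 × 0.02 = 1.56.

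- SE without country = √(2 × 0.18 × 0.82/648 × (1 + 35 × 0.02)) = 0.0278.
- If country carries a share f of the between-centre variance, the adjusted SE uses ICC × (1 − f). At f = 0.5 it is √(2 × 0.18 × 0.82/648 × (1 + 35 × 0.01)) = 0.0248.
- Because country is balanced, the true spread of the estimate is close to 0.0248 under either model. Only the reported SE differs.
- Power without country = Φ((0.08 − 1.96 × 0.0278)/0.0248) ≈ 85%.
- Power with country = Φ((0.08 − 1.96 × 0.0248)/0.0248) ≈ 90%.
- One-sided error without country = 1 − Φ(1.96 × 0.0278/0.0248) ≈ 1.4%, against a nominal 2.5%.

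Shares of 25%, 50% and 75% correspond to country gaps of 2 × √(f × 0.02 × 0.18 × 0.82) = 5.4, 7.7 and 9.4 percentage points.

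**Phase 4, simulation.** Centre proportions were beta-binomial, with linear regression on them, a t reference and 20,000 trials per cell:

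| Country share of between-centre variance (assumed) | Power without country | Power with country |
|---|---|---|
| 25% | 80% | 84% |
| 50% | 82% | 88% |
| 75% | 84% | 92% |

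A repeat run gave 81% v 84%, 82% v 89% and 83% v 92%.

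**Phase 3, simulation of the planned type of model.** A random-intercept logistic model was fitted to 18 v 9 centres with 32 analysed per centre (40 × 0.8) and 1000 trials per row. Here the ICC of 0.02 applies within country, so the country difference comes on top of it:

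| Country odds ratio (assumed) | Power without country | Power with country |
|---|---|---|
| 1.0 | 90.9% | 91.3% |
| 1.25 | 90.6% | 91.4% |
| 1.5 | 90.7% | 92.3% |
| 2 | 85.6% | 92.5% |
| 3 | 78.7% | 92.5% |

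Monte Carlo error is about 1 point. At an odds ratio of 2, the mean reported SE is 0.328 without country and 0.288 with it (+14%).

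These logistic runs use a normal reference, which is too liberal with 27 centres. With no treatment effect and no country difference, rejection was 7.7% without the term and 8.2% with it. The powers therefore compare the two models and should not be read as absolute. In a centre-level t-test simulation, type I error without country fell to 3.4% (odds ratio 2) and 2.1% (odds ratio 3), against about 5% with it, which confirms the direction.

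**Cost if country does not matter.** Across the runs the country term cost about half a point of power or less. Two centre-level terms leave 23 of 25 degrees of freedom in phase 3 and 32 of 34 in phase 4.

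Centre volume was not simulated, because the article gives no figure for its effect.

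**The case against.** The strongest reply is that the omission is inferred. The sentence on categorical outcomes is not an exclusive list. It places logistic regression inside a framework that the preceding sentence has just given covariates, and the Abstract's generalised linear model could cover a binary outcome. The detailed covariate list may sit in the full protocol or SAP, which are not shown. This stands to the extent that a reader might infer that the primary model has only treatment and cluster terms, and the article does not establish that. What remains is that the article does describe a model for this type of outcome and attaches covariates only to the other type.

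A reader might also infer that the trial loses power against its plan. The documents do not support that. If the ICC of 0.02 already contains between-country variation, unadjusted power does not fall as country's share grows (80%, 82% and 84% in phase 4), and the difference is a gain forgone. Only if 0.02 is a within-country value does unadjusted power fall, as in the phase 3 table. The article does not say which it is. Likewise, phase 4 power of about 82% on these inputs arises with no country effect at all, so this point does not explain it.

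Two further readings fail. Between-centre variance is not the main limit on phase 3 precision: its share is 0.02/(0.02 + 0.98/32) ≈ 40%. And although day-0 items such as "Tobacco use and quit history" are collected, no documented figure supports a particular gain from adjusting for them.

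Finally, the error is on the safe side: omitting country makes the test conservative and creates no false-positive inflation.

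**Conclusion.** The point holds as a free improvement. As worded, the article does not carry its allocation factors into the model described for the primary outcome, and doing so would cost almost nothing.

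The benefit depends on a country difference that the documents do not give. Over the assumed ranges it is about 2 points of power or less in phase 3 up to an odds ratio of 1.5 and about 7 points at 2. In phase 4 it is about 4 to 8 points for a country share of 25% to 75% at a total ICC of 0.02. With no country difference there is nothing to gain. Mechanism and direction are firm; the size is conditional. The phase 3 figures are less secure, because nine control centres cannot be split evenly by country and centre-level runs at a total ICC of 0.02 were sensitive to where the odd centre falls.

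**What to change.** In Inferential statistics, state that the mixed-effects logistic model for verified abstinence, in both phases, includes country and average monthly TB patients as fixed effects alongside the centre random effect. Use the same terms in the multiple imputation model, and keep the model without covariates as a sensitivity analysis.

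Day-0 smoking status and nicotine dependency, both already scheduled in Table 2, may be added if pre-specified, but no size of gain should be claimed for them.

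The change is wording only. Both factors are known when centres are allocated, so no new data are needed. The downside is two centre-level degrees of freedom, about half a point of power or less if the factors are not prognostic. Because removing the conservatism also removes a cushion, the reference distribution for a small number of centres should be settled in the SAP at the same time.
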